#### Data collection

Consented participants will be allocated a study ID number that identifies their participating school and unique identifier; this allows for pseudo-anonymisation and confidentiality of data. The data will be collected by suitably trained, qualified and calibrated NQD, supervised by the RiY research team from the University of Leeds. Data Sharing Agreements will be put in place with each participating school/college to allow General Data Protection Regulation (GDPR) compliant transfer of study-relevant data between each school and the University; the data handling procedures will be in accordance with the GDPR Act 2018.

##### Group 1 Participants-peer recipients

The following assessments for student participants aged between 11 and 13 years will be completed at baseline and post-intervention:

Dental assessment to record DMFT/dmft (at baseline only), Plaque index and Gingival Index. Each participant will brush their teeth allowing assessment of toothbrushing skills; ‘bleeding on probing’ is not influenced by precleaning teeth and is a proxy marker for longer term behavioural change. These are used in the feasibility trial as interim clinical markers of success but in the full trial there will be longer term assessment using the ICDAS (International Caries Detection and Assessment System (ICDAS) scores/DFMT as measure of effect on caries prevention) [46].Complete questionnaires:oAdapted WHO Oral Health Questionnaire for children [45] (Leeds online surveys/Google forms or paper form according to school preference). It is a widely used and validated tool enabling countries to conduct standardised oral health surveys that are comparable internationally.oQuiz about oral health knowledge, attitudes and behavioursSaliva sample collection as part of YUK Oral Bugs citizen science project. Consented participants will provide a saliva sample by chewing on paraffin wax and drooling into a tube for approximately 5 min to collect approximately 5 ml.

##### Group 2 RiY-peer leaders

RiY-peer leaders will be invited to complete an online survey which will take approximately 15 min to complete.Participants will be invited to a focus group or interview to explore their experiences of being involved with the RiY programme.The RiY-peer leaders will be invited to undergo optional dental exams and assessments and saliva collection (the same as group 1 years 7 and 8 participants). This is to explore the added benefits/impacts of the programme to their own oral health. Data collection will occur at baseline and follow-up in line with Group 1 participants.

##### NQD

NQD will be invited to take part in feedback sessions to fulfil feasibility outcomes.NQD will be invited to complete an online survey. The results of the online survey will facilitate topic guide creation for further focus group discussion.NGD will only be considered ‘participants’ to take part in the feedback sessions of the programme. NQD can participate as members of the research team without participating in these feedback sessions. Consent will be required to participate in these feedback sessions.

#### YUK-saliva processing

Tubes of saliva will be labelled, transported, and processed according to DenTCRU, University of Leeds local working instructions for oral microbiome analysis. Participants will not be identifiable on these labels. These will ensure compliance with GOV.UK packaging and transport requirements UN 3373 P650 standard [47].

The saliva samples will be stored in a University of Leeds DenTCRU −80 Freezer or −20 Freezer for RiY processing for shotgun or 16S (commercial) sequencing. 16S sequencing summary compositional oral microbiome reports will be generated and SPSS software or other specialist software will be used for statistical/descriptive analysis of data in addition to the production of heatmaps using the R software package.

Samples will be subjected to shotgun/16S profiling using a commercial platform such as Illumina MiSeq technology or equivalent delivered via an extraction kit or equivalent resource. The data will be available for scientists and processed bioinformatically.

#### YUK biofeedback

A summary of simplified oral microbiome stomatypes will be used for the school biofeedback session. This will be simplified aggregate data that ensures confidentiality and ensures no stigmatisation of any individuals. It aligns with the YUK-Oral Bugs reinforcement session to relay information relating to any changes in bugs related to participants receiving the intervention from their newly acquired knowledge, skills and behaviour of oral health and tooth brushing compared to their baseline sample. Having control group samples will allow identification of any additional influence relating to oral health in the school background.

The feasibility of producing school summary aggregate biofeedback data in a timely manner will be assessed. Stakeholders will be asked to provide comment.

#### Data analysis

The outcome data of this feasibility trial will be reported in accordance with CONSORT 2010 statement extension to randomised pilot and feasibility trials [48].

#### Quantitative analysis

Participant data will be entered electronically on a password protected Microsoft Access database (Trademark of MICROSOFT Corporation, [name]) stored securely on the University of Leeds cloud server and accessed via encrypted University of Leeds devices only. Data will be pseudo-anonymised by assigning a unique identification number to each participant. The final data set will reside in DenTCRU, University of Leeds. Data sharing agreements are in place with all schools to allow participant details to be shared and stored. Descriptive analysis will be undertaken by research statisticians using SPSS software. Planned interim analysis will be undertaken to address feasibility outcomes and compare against the progression criteria. The findings will inform possible changes required to improve operational delivery of the trial.

Feasibility, the primary outcome of this study, will be evaluated by calculating the percentage of recruited participants from the target recruitment number of participants overall (recruitment) and the percentage who complete the intervention and have follow-up data (retention).

#### Qualitative analysis

Recordings of semi-structured interviews and focus groups undertaken as part of the evaluation process will be transcribed verbatim. Data familiarisation, coding and interpretation will be conducted independently by two members of the research team to identify relevant themes. Qualitative findings will be utilised alongside quantitative outcomes related to process evaluation to explore how RiY was experienced by participants and any changes to help improve the intervention. The plan is for summary trial results to be shared with the schools.

#### Adverse events and serious events procedures

The study is covered by the University of Leeds Public Liability Insurance.

#### Serious adverse events and adverse events

Adverse events (AE) and serious adverse events (SAE) related to the study intervention will be collected and recorded in the adverse event log.

Participants may experience minor discomfort, becoming upset or may experience minor bleeding as a result of the dental exam. Similarly, during the trial, participants may also experience unrelated health incidents. These events will not be recorded as part of the safety reporting of the intervention. We only seek to record those that could be related and unexpected.

An event is defined as ‘related’ if the event was due to the administration of any research procedure. The relatedness of an event will be reviewed by the principal investigator.

#### Reporting adverse events

Details of any SAEs or AEs will be reported to the PI by the research team. Only details of any SAEs that are required to be reported to the Research Ethics Committee, i.e. SAE events which are related to taking part in the study and are unexpected, and AEs that are related and unexpected will be recorded using a trial adverse event form. The AE reporting period for this trial begins as soon as the participant consents to be in the study and ends at the final data collection point.

#### Reporting urgent safety measures

Safety issues will be reported to the DREC in the annual progress report. An annual summary of all events will also be reported to the Sponsor on request. Expedited reporting of events to the DREC and the Sponsor will be subject to current DenTCRU Standard Operating Procedures (SOPs) and Sponsor requirements.

#### Suspected serious pathology

In rare events where serious dental or oral pathology has been suspected (for example, oral cancer, sepsis or unexplained swelling) and identified during clinical examination, the Chief Investigator or Principal Investigator will discuss with a second colleague in line with good practise, to decide on the most appropriate person for the participant to be referred to. If the common consensus is to refer the participant, the school will be contacted and DenTCRU will work closely with the school and school nurse to ensure the participant receives the help in their best interest and safety.

#### Safeguarding

RiY has strict safeguarding procedures in place that have been ethically approved. In summary, our process is that any concerns identified during the dental checks will be communicated directly to the School safeguarding lead. The school has clear instructions and a detailed flow diagram to follow depending on whether the child has a registered dentist or not. It is the school’s role to liaise with parents/guardians.

## Discussion

This feasibility study is a result of the need for a sustainable method to address poor oral health in secondary school students, reduce oral health inequality in areas of high social deprivation and increase aspiration and STEM (Science, Technology, Engineering and Maths careers) opportunities for 16–18-year-old first-in-family students [25]. Data relating to raising aspirations of the peer leaders will enable the wider impact of participating in the RiY programme to be captured. In these schools, the students often lack parental-initiated opportunities for work experience and university connections to raise aspirations to apply for higher educational continued education. The impact on peer leaders of participating in the RiY Programme will be explored in YE doctoral studies.

The RiY trial is one of the first school-based peer-led interventions targeting oral health behaviour change in adolescents in the UK. It is also a pioneering evaluation of oral microbiome data being collected and analysed from at-risk adolescents. Many oral health prevention programmes exist and are implemented in schools by either teachers or health and social-care workers [49], but RiY is novel in its peer-to-peer approach and the benefits proposed are likely to affect participants and support NHS workforce development by engagement of the NQD in leadership and research opportunities.

A strength of this feasibility study is the recruitment of several local schools across the local area as it improves the generalisability of the findings in the West Yorkshire region. The authors will work closely with participating schools to ensure that the intervention can be incorporated into the curriculum with minimal disruption to the timetable.

The use of NQD could be seen as a limitation of the study data collection. However, great lengths have been taken to train, calibrate and up-skill them to be competent assessors. They are working completely within their professional scope; plaque scoring and bleeding on probing are all commonly used clinical indices. If RiY progresses to a full trial, follow-up would require more complex ICDAS scoring and full consideration would be given to having trained and calibrated clinicians for ICDAS scoring to ensure the highest standards of data integrity. Nonetheless, NQD offer a fantastic sustainable approach to deliver school-based dental public health research. The benefits to these NQD are being explored further in a separate study by NF and NH.

The findings of this trial will inform the design of a future definitive randomised controlled trial if it is shown to be feasible. The RiY concept is expandable from Yorkshire to other geographical areas as ‘RAISED in … *[insert new locality]*’ to provide local ownership, relatability, and pride in the programme, supported by NQD in these localities could offer a sustainable approach that warrants further health economic evaluation. The current feasibility protocol is focused towards advancing mechanistic understanding with the inclusion of YUK. Preliminary health economic assessments are not possible within this RiY feasibility trial due to current funding constraints but this will be important to include in the definitive trial. At an upstream level, this could be adopted to improve oral health prevention policies and guidance to reach at-risk adolescents in areas of high oral health inequality.

Progression to main trial will be based mainly on recruitment and retention, but with other considerations that may influence modifications or remedial action, if needed prior to progression (Table 2). Facilitators and barriers to recruitment and data collection will be identified and strategies will be refined and tested in subsequent year 2 (3 if required) to further inform the main trial.

**Table 2 Tab2:** Progression criteria to progress to full trial

	**Automatic progression**	*Progression with modification if appropriate*	*Remedial action with key stakeholders/advisory group*	
**Recruitment** % of target number of 11–13-year-old participants recruited (~240 participants (~*n* = 48/school)	** > 75%**	> *50–*< *75%*	< *50%*	
Recruitment of schools *n* = 4 (numbers enrolled)	** > 75%**	> *50–*< *75%*	< *50%*	
**Retention** % of recruited participants with follow up data	** > 65%**	> 40–< 65%	< 40%	
% of recruited schools with follow up data	** > 65%**	> 40–< 65%	< 40%	
**Randomisation:** % of contamination in the control group (whether feasible to randomise by class or by school)	** > 75%**	> *50–*< *75%*	< *50*	

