**Methods:**

This is a UK school-based, assessor-blinded, parallel two-arm randomised controlled feasibility trial with a preliminary interim assessment in advance of progression to a larger scale trial in the future. The trial aims to recruit *n* = ~240 11–13-year-old participants and *n* = ~50 16–18-year-old peer leaders across five schools/colleges in West Yorkshire. The primary outcomes are related to feasibility in terms of recruitment and retention of participants, and the ability to deliver the intervention. The secondary outcomes include the oral health of participants (knowledge, attitudes and behaviour, plaque and gingival index) and process evaluation.

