### Trial design

The RiY feasibility trial is a UK school-based, assessor-blinded, two-arm randomised controlled trial (RCT). The feasibility trial will be conducted over two to three school academic years with an interim analysis planned at the end of Academic Year 1. The findings of the interim analysis will inform possible changes required to improve operational delivery in subsequent academic years. The study will be carried out in secondary schools in West Yorkshire serving a diverse population with high dental needs. Up to five participating schools will be targeted for this study.

This intervention will be a multicomponent complex intervention comprising two main parts: (1) a short classroom-based oral health education session including three interactive workshops; (2) a reinforcement session including three interactive workshops (YUK-Oral Bugs). Participants in the control group will receive the classroom-based oral health education session after the final follow-up assessments have been completed to avoid contamination of the data collection, but access will be ensured for all to the main RiY session, so that no one is disadvantaged.

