#### Study population and setting

A feasibility trial allows identification of key challenges with implementing a complex intervention and operational delivery in the school setting that is unfamiliar with undertaking RCTs. This trial aims to recruit up to five UK secondary schools with an integrated Sixth Form/Sixth Form Colleges and their feeder secondary schools. A formal sample size calculation was not used for this feasibility trial. Rather a pragmatic approach will be adopted informed by the systematic review of Parker et al. [37] looking at health interventions in schools, guidelines developed by Teresi et al. [38] for designing feasibility and pilot studies, and the BRIGHT trial that worked with similar aged adolescent participants delivering an oral health intervention in schools randomised by forms within year groups [5] using a target of *n* = 60 per year group/school. The focus in RiY is on practical considerations, needing to work within a tight budgetary constraint, but considering primarily the number of participants needed to reasonably evaluate feasibility goals of recruitment and retention of students alongside collecting process evaluation data on logistical components of working in school settings located with catchment to an underserved community with high oral health inequalities and often high ethnic diversity, alongside needing to assess the training of peer leaders that is a novel delivery approach of RiY’s oral health promotion. For 11–13-year-old participants, the target recruitment will be at least four classes per school with all students invited (class size is typically *n* = ~30 students/class) achieving *n* = ~240 participants (~*n* = 48 11–13-year-old participants/school); it is expected that this sample size will provide sufficient data to inform a future main trial. This trial will work closely with teachers to ensure that the intervention has minimal interruption to normal school curriculum and timetabling.

For 16–18-year-old peer leaders, the target recruitment will be *n* = ~50 peer leaders (10–12 participants per school/college).

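### Table 2 counts school recruitment out of four, but its participant target of ~240 at ~48 per school, and the rest of the protocol, assume five schools

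*Protocol article*

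**What the plan says.** The Abstract (Methods) states the overall aim: "The trial aims to recruit *n* = ~240 11–13-year-old participants", and places it "across five schools/colleges in West Yorkshire". Under Trial design the number is a ceiling: "Up to five participating schools will be targeted for this study". Study population and setting repeats that ceiling ("This trial aims to recruit up to five UK secondary schools") and gives the make-up of the target as "achieving *n* = ~240 participants (~*n* = 48 11–13-year-old participants/school". The same section sets a peer-leader target of about 50, at 10 to 12 per school or college.

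Table 2, in the Discussion, holds the progression criteria. The participant row is the percentage "of target number of 11–13-year-old participants recruited (~240 participants (~*n* = 48/school". The row beneath it is "Recruitment of schools *n* = 4 (numbers enrolled". Both rows use the same bands: automatic progression above 75%, progression with modification above 50% and below 75%, and remedial action below 50%.

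**The concern.** Two adjacent rows of one decision table assume different numbers of schools. A total of 240 at 48 per school needs five, but the school row is counted out of four.

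The table matters because the Discussion makes progression depend mainly on recruitment and retention. The Quantitative analysis section makes recruitment against target part of the primary outcome. An unreconciled denominator leaves it unclear what counts as full school recruitment. It also alters how demanding the participant threshold is if only four schools join.

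**Working it through.** **Inputs.** Total ~240 and ~48 per school (Study population and setting; Table 2). Schools: five (Abstract), up to five (Trial design; Study population and setting), four (Table 2). Peer leaders: ~50 at 10–12 per school. Invitations: at least four classes of about 30 per school.

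**1. Reproduce the target.** Schools × pupils per school: 5 × 48 = 240, exactly as stated. With Table 2's four schools, 4 × 48 = 192, and 192/240 = 80%.

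**2. Cross-check on peer leaders.** Five schools give 5 × 10 to 5 × 12 = 50 to 60. Four give 4 × 10 to 4 × 12 = 40 to 48. The target of ~50 lies inside the first range and just above the second, so it fits five better, although the approximate figure does not settle the matter alone.

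**3. Apply the bands at each number of enrolled schools**, with each school delivering 48:

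| Schools | School row out of 4 | School row out of 5 | Pupils, % of 240 |
|---|---|---|---|
| 1 | 25%, remedial | 20%, remedial | 48, 20%, remedial |
| 2 | 50%, no band | 40%, remedial | 96, 40%, remedial |
| 3 | 75%, no band | 60%, modification | 144, 60%, modification |
| 4 | 100%, automatic | 80%, automatic | 192, 80%, automatic |
| 5 | 125%, automatic | 100%, automatic | 240, 100%, automatic |

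Out of four, the only values up to full recruitment are 25, 50, 75 and 100%. None lies strictly between 50 and 75, so the middle band is unreachable, and two of the four values sit on cut-points that no band covers. Out of five, the school row and the participant row agree at every count.

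**4. Participant threshold with four schools.** Exceeding 75% of 240 means more than 180, so at least 181.

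- Four schools: 181/4 = 45.25 per school, and 45.25/48 = 94%.
- Five schools: 181/5 = 36.2 per school, and 36.2/48 = 75%.

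**5. Where the choice of denominator changes the band.** With four schools enrolled:

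- 145 to 179 pupils is modification against 240 (60.4% to 74.6%) but automatic against 192 (75.5% to 93.2%). For example, 40 per school gives 160: 66.7% of 240, 83.3% of 192.
- 97 to 119 pupils is remedial against 240 (40.4% to 49.6%) but modification against 192 (50.5% to 62.0%).

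**The case against.** The strongest reply is that the rows do not conflict in practice. Four of four schools scores 100%, and four schools at 48 each gives 80% of 240, so both rows allow automatic progression. A reader might infer from the mismatch that the two criteria contradict each other. That goes too far: they measure different things, and both pass at full delivery. What remains is a thinner margin on the participant row and a school row whose bands do not work out of four.

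A reader might also infer that 240 is itself unsound, because Study population and setting contains the phrase "using a target of *n* = 60 per year group/school". The documents do not support this. The phrase closes a clause about a cited school oral-health trial, one of several sources for a pragmatic size, and reads most naturally as that trial's target. This trial's own figure is stated separately as ~48. That 4 × 60 also equals 240 hints at where the four came from, but this is only an inference.

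Nor is 48 a cap. About 4 × 30 = 120 pupils are invited per school, so 48 is a 40% yield. Four schools would invite about 480, and 181/480 is about 38%, so 181 pupils from four schools is attainable.

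Finally, up to five is a ceiling, so a working target or minimum of four is conceivable. Table 2 does not say so. It uses four as the denominator of a percentage while keeping 48 per school in the row above.

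The consequences are also limited: the numbers are approximate, no formal sample size was calculated, and no band stops the programme outright.

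**Conclusion.** The point holds as a four-versus-five denominator mismatch in Table 2. The four disagrees with the row above it, the Abstract and the Methods; 240 stands as 5 × 48.

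The effect is modest. On the school row, three or two enrolled schools receive no classification and the middle band is empty. On the participant row, four enrolled schools must each reach about 94% of the per-school target for automatic progression, against 75% with five. The 94% assumes equal recruitment across schools and ~48 as the expected yield. The band changes in step 5 arise only if four schools enrol and average fewer than 45.25 pupils each. Randomisation, conduct and the analysis of the clinical outcomes are unaffected.

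**What to change.** Change the school-recruitment row of Table 2 to n = 5. Then 4/5 (80%), 3/5 (60%) and 2/5 (40%) fall into the automatic, modification and remedial bands.

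If four schools is the real target, say so in the Abstract, Trial design and Study population and setting, and restate the participant row to match: ~192 at 48 per school, or 240 at 60 per school. In that case, also state which band exactly 75% and exactly 50% belong to, because three and two schools out of four land there. If four was meant as a minimum, label it as one.

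A few words making clear whose target the 60 per year group was would remove the ambiguity, but that is secondary.

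The cost is one table cell for the simple correction, or a few figures for the alternative. It should be settled before interim results are compared with Table 2. If that comparison has already been made, the report should state which denominator was used.

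### Table 2 sets school recruitment on n = 4 with open-ended bands, so enrolling 3 or 2 schools gets no verdict, the middle band is unreachable, and 4 conflicts with the five schools given elsewhere

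*Protocol article*

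**What the plan says.** Under Discussion, the protocol article states that "Progression to main trial will be based mainly on recruitment and retention", adds that other considerations may lead to modification or remedial action, and refers to Table 2 for the criteria. Under Quantitative analysis, the planned interim analysis is to be compared against those criteria.

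The Table 2 rows that matter here are:

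- School recruitment: "Recruitment of schools *n* = 4 (numbers enrolled", with automatic progression above 75%, progression with modification above 50% and below 75%, and remedial action below 50%.
- School retention: the percentage "of recruited schools with follow up data", with bands above 65%, above 40% and below 65%, and below 40%.
- Participant recruitment: the percentage "of target number of 11–13-year-old participants recruited (~240 participants (~*n* = 48/school", with the same bands as school recruitment.

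Every inequality is strict, and no text assigns a boundary value to a band.

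On the number of schools, the Abstract (Methods) speaks of five schools or colleges. Trial design says "Up to five participating schools will be targeted for this study", and Study population and setting also gives five as the upper limit.

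**The concern.** On a near-continuous scale, an open boundary rarely matters. School counts take only a handful of values, and with a denominator of four both cut-points fall on attainable counts. A row meant to give three verdicts then gives two, and is silent on the two counts in between. If three or two schools enrol, someone must decide after seeing the count which side of the line it belongs on. Fixing the criteria in advance is meant to prevent that.

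The number 4 is itself in doubt, because the rest of the article works with five. A reader cannot tell which denominator the interim comparison will use, and the two give different verdicts for the same number of schools.

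**Working it through.** **Inputs.** The school denominator of 4, the participant target of about 240 at about 48 per school, and the band limits all come from Table 2. The alternative denominator of 5 comes from the Abstract and, as an upper limit, from Trial design and Study population and setting. No power, error rate or effect size enters: the article says "A formal sample size calculation was not used for this feasibility trial".

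**Implied number of schools.** 240 / 48 = 5, whereas 4 × 48 = 192. So the participant row and the school row of the same table use different numbers of schools.

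**School recruitment.** Each count k is converted to k/n and classified by the printed strict inequalities.

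| Schools enrolled | n = 4 | Verdict | n = 5 | Verdict |
|---|---|---|---|---|
| 5 | 125% | automatic | 100% | automatic |
| 4 | 100% | automatic | 80% | automatic |
| 3 | 75% | none | 60% | modification |
| 2 | 50% | none | 40% | remedial |
| 1 | 25% | remedial | 20% | remedial |
| 0 | 0% | remedial | 0% | remedial |

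With n = 4, the middle band needs a count strictly between 0.50 × 4 = 2 and 0.75 × 4 = 3, and no such count exists. As up to five schools may enrol, 2 of the 6 possible counts (33%) are unclassified. With n = 5, none is.

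**Effect of the repair at n = 4.**

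- Closing upward (at least 75%; at least 50% and below 75%; below 50%): 3 schools is automatic and 2 is modification.
- Closing downward (above 75%; above 50% up to and including 75%; 50% or less): 3 schools is modification and 2 is remedial.

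Both counts change verdict with the choice. At n = 5 the two repairs give identical verdicts for recruitment.

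**School retention as printed.**

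- Five recruited: 5/5 and 4/5 (80%) are automatic, 3/5 (60%) is modification, 2/5 is exactly 40% and has no verdict, and 1/5 (20%) and 0/5 are remedial.
- Four recruited: 4/4 and 3/4 (75%) are automatic, 2/4 (50%) is modification, and 1/4 (25%) and 0/4 are remedial. There is no gap.

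**Participant rows.** The recruitment gaps are the single values 0.75 × 240 = 180 and 0.50 × 240 = 120. If 240 are recruited, the retention gaps are 0.65 × 240 = 156 and 0.40 × 240 = 96.

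**The case against.** The strongest reply is that the true denominator is five, and that with five the printed recruitment bands work for every count. This stands as far as it goes: the strict inequalities alone do not break the recruitment row. A reader might infer that the inequality signs are the whole fault, and the enumeration at five does not support that. But the row prints 4, and wording that allows up to five schools does not override it. If five was meant, the row still has to be corrected.

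A second reply is that four may be deliberate. Study population and setting mentions a target of 60 per year group and school, and 4 × 60 is also 240. That shows the total alone does not settle the matter. Table 2, however, states 48 per school, and if four is intended both boundary gaps apply.

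A third reply concerns consequence, and it largely stands. Table 2 has no stop band, school recruitment is one of several rows, listed considerations can modify the outcome, and further school years are available for refinement. A boundary value leaves a choice between two neighbouring bands. A reader might infer that progression as a whole is left undecided, but the article does not support that.

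A reader might also infer that losing one of four enrolled schools gets no verdict. Losing a school after enrolment is judged in the retention row, where 3/4 = 75% is above 65% and therefore automatic. The recruitment gap arises only when fewer schools enrol. Nothing in the article says how likely that is.

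**Conclusion.** The point holds as a moderate defect in a stated decision rule. Taking n = 4 and the signs as printed, enrolling three or two schools has no verdict and the middle band cannot be reached. That is 2 of the 6 counts possible when up to five schools may enrol. Quoting 2 of 5 would leave out the fifth school that the design allows.

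The cause is n = 4 combined with open boundaries, and n = 4 also disagrees with the Abstract and with the 48 per school in the same table. With five schools the recruitment row has no gap, and the retention row has one, at 2 of 5.

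The gaps in the participant rows are single values against an approximate target and are minor. No effect estimate, error rate or safety matter depends on this point.

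The conclusion assumes that n = 4 is the denominator for the row's percentages, which is its natural reading, and that the inequality signs are as the authors intended.

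**What to change.** 1. Settle the number of schools (4 or 5), and use it in the school recruitment row, the participant row, the Abstract and the design sections.

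2. State which band owns each boundary. One option is at least 75%, at least 50% and below 75%, below 50% for recruitment, with at least 65%, at least 40% and below 65%, below 40% for retention. Closing upward in this way is the more lenient choice and should be acknowledged as such.

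3. Write the school rows as counts, separately for recruitment and retention. With the bands closed upward:

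| Row | Automatic | Modification | Remedial |
|---|---|---|---|
| Recruitment, target 5 | 4–5 | 3 | 0–2 |
| Retention, 5 recruited | 4–5 | 2–3 | 0–1 |
| Recruitment, target 4 | 3–4 (or 5) | 2 | 0–1 |
| Retention, 4 recruited | 3–4 | 2 | 0–1 |

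The recruitment counts for five schools cannot be reused for retention, because 2/5 = 40% is remedial in the first and modification in the second.

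4. Make the change before the interim comparison with the criteria.

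The cost is edits to one table, plus a consistent school number in the text. If the number of schools itself changes, the participant target per school must be brought into line. No data collection or analysis method changes.
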